### 2.8.2 Secondary outcomes: adverse outcomes, mechanisms underlying improved reactive stepping, functional balance, and falls efficacy

Adverse outcomes will be monitored, recorded, and reported according to the ExHaRM protocol. The physiotherapist will observe and monitor participants for adverse outcomes during the sessions (e.g., injuries, pain, expressions of fear/anxiety). Participants will also be prompted to report any adverse outcomes they experienced after the session at the subsequent session by asking “since our last session, have you experienced any harmful or undesirable outcomes, whether or not you think they were caused by exercise?”. Adverse outcomes will be documented in Epic using the Common Terminology Criteria for Adverse Events (version 5.0; CTCAE). Psychological adverse outcomes (i.e., fear and anxiety related to the perturbations) are not included within the CTCAE, and will be documented separately. Documentation will include a narrative description of the adverse outcome, adverse outcome category, severity, whether the adverse outcome is attributed to the study intervention/procedures, and impact of the adverse outcome on the study. The physiotherapist will ensure that participants receive appropriate care when adverse outcomes require immediate attention (e.g., injuries); depending on the severity of these adverse events, the participant may be withdrawn from the study. The physiotherapist may modify the intervention in response to less severe adverse outcomes (e.g., reducing the number of perturbations due to fatigue, mild pain, or fear/anxiety).

The initial step reaction may be ineffective for several reasons (e.g., too short or slow), necessitating additional steps to recover balance. To explore the mechanisms underlying improved reactive stepping with practice, we will also obtain the following outcomes from the force plates and motion capture system during the backward-fall perturbations: step initiation time (from perturbation onset to foot off), step execution time (from foot off to foot contact of the first step), step length (difference in foot position from foot off to foot contact), braking impulse (antero-posterior shear force generated over time on step contact), and mechanical margin of stability at foot contact. Margin of stability is the distance between the extrapolated centre of mass (incorporating centre of mass position and velocity) and the edge of the base of support. Low values indicate that the centre of mass is close to and/or moving quickly towards the edge of the base of support and, therefore, that the person is close to falling (i.e., less stable).

Functional balance will be assessed using the mini-Balance Evaluation Systems test (mini-BEST), which is a 14-item observational rating scale that assesses balance systems, including reactive balance control. The mini-BEST has good inter- (ICC=0.96) and intra-rater reliability (ICC=0.97) in chronic stroke. The mini-BEST reactive balance control sub-scale will provide further support for transfer of training effects to untrained contexts.

We will use additional recommended secondary outcomes from the Core Outcome Set for Evaluating Mixed-Diagnosis Falls Prevention Interventions; that is: 1) fall incidence; 2) injurious fall incidence; 3) quality of life (5-level EuroQoL health status measure; EQ-5D-5L); 4) falls self-efficacy (Falls Efficacy Scale International; FES-I); 5) fear of falling; and 6) activity curtailment due to fear of falling. These outcomes, except for the FES-I, are collected to harmonize outcomes with other fall prevention studies and will not be analyzed to address a specific study objective or hypotheses. To assess fall incidence and injurious fall incidence, participants will be asked to report falls (“an event that results in a person coming to rest unintentionally on the ground or other lower level”) for 12 months post-training. Participants will be provided with stamped, addressed postcards

[figure not shown]

**Figure 4: Illustration of possible learning curves for the three groups.** Learning curves were created using expected pre-training average of 3-4 steps, and post-training average of 1-2 steps for the trained groups.

to mail to the research team every month for 1 year post-training. Postcards will contain a calendar, on which participants will record falls. The blinded research assistant will call participants who do not return the postcard to determine if any falls occurred. The research assistant will also contact participants reporting a fall to complete a short questionnaire determining the cause and consequences of the fall (e.g., injuries; Appendix E). This method is considered the ‘gold standard’ for fall reporting and has been successfully used by our team. The 5-level EuroQoL health status measure (EQ-5D-5L) asks participants to rate their health in five dimensions (mobility, self-care, usual activities, pain/discomfort, and anxiety/depression) on a five-point scale and their overall health state on a scale from 0-100. The EQ-5D-5L has good-to-excellent test-retest reliability across several populations (ICC: 0.69-0.93). The FES-I asks participants to rate their concern about falling while performing 16 everyday tasks. The FES-I shows excellent test-retest reliability (ICC=0.97) in people with chronic stroke. Fear of falling and activity curtailment due to fear of falling will be assessed with two questions (“are you afraid of falling?” and “do you think fear of falling has made you cut down on any activities that you used to do?”).

The mini-BEST, EQ-5D-5L, FES-I, fear of falling, and activity curtailment due to fear of falling will be assessed pre- and post-training. Additionally, the EQ-5D-5L, FES-I, fear of falling, and activity curtailment due to fear of falling will be repeated via telephone at the end of the 1-year falls monitoring period (Figure 1).

### 2.8.3 Cohort descriptors

The following information will be recorded at study enrolment to characterize the cohort: age, sex, gender identity, height, weight, time since stroke, lesion location, pre-morbid medical history, prescription medications, the National Institutes of Health Stroke Scale (stroke severity), Chedoke-McMaster Stroke Assessment foot and leg scores (motor impairment), and the Nielsen gender questionnaire. Cohort descriptors will be obtained directly from participants, or from Epic (Appendix F).

## 2.6 Sample size justification

Our primary outcome is learning rate. The sample size for each group was estimated as  $\lambda/\Delta$ , where  $\lambda$  was obtained from tables for 3 groups using probability of a Type 1 error ( $\alpha$ ) of 0.05, probability of a Type II error ( $\beta$ ) of 0.2; therefore,  $\lambda$  of 9.64 was used. Additionally:

$$\Delta = \frac{1}{\sigma^2} \sum_{i=1}^k (\mu_i - \bar{\mu})^2$$

where  $\sigma$  is the standard deviation,  $k$  is the number of groups (3),  $\mu_i$  is the mean for each groups and  $\bar{\mu}$  is the mean for all groups combined. From pilot data, we estimate a standard deviation of 9.7 for the learning rate. People with stroke typically require 3-4 steps to regain stability following the perturbation magnitudes used in the proposed study. Due to the mechanical challenges of the perturbation, at minimum 1 step is required to respond to the perturbation (i.e., young healthy adults would take 1 step to respond to the perturbation). Therefore, an improvement from 3-4 steps pre-training to 1-2 steps post-training is considered clinically meaningful, and a much larger effect size would likely not be possible. From previous studies an improvement from taking, on average, 3-4 steps pre-training to 1-2 steps post-training is feasible. Simulating learning rates between these data points (Figure 5), we expect that learning rates of approximately 0.4 ( $\mu_1$ ), 2 ( $\mu_2$ ) and 10 ( $\mu_3$ ) for the high-intensity, moderate-intensity, and walking control groups, respectively, would show meaningful differences between the three groups. Therefore,  $\Delta$  was calculated as 0.56, giving a target sample size of 17 per group or 51 participants total. To account for a ~20% rate of withdrawal, we will aim to recruit 21 participants per group, or 63 participants total. Enrolment will stop when 51 participants have completed the retention test, or 63 participants have been enrolled, whichever happens first.

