### 1.2 Objectives and hypotheses

The purpose of this study is to determine the optimal intensity of RBT post-stroke. The 'optimal' intensity is the intensity that improves reactive balance control in fewer sessions, without any apparent negative consequences (i.e., no increase in adverse outcomes). We expect that high-intensity training (50% above the multi-step threshold) will improve reactive stepping ability faster than moderate-intensity training (at the multi-step threshold). If the first reactive step is not effective in avoiding a fall after a loss of balance, additional steps must be taken; therefore, the number of steps needed to recover from a loss of balance is a global indicator of the effectiveness of balance reactions. We will assess reactions to novel, untrained, balance perturbations throughout training, and calculate the rate of decline in average number of steps taken to recover balance (i.e., learning rate). Retention of learning will be assessed one week post-training. Our primary hypotheses are:

- 1) Adaptation rate will be faster for high-intensity RBT than moderate-intensity RBT;
- 2) Adaptation rate will be faster for both RBT groups than a walking control group; and
- 3) Both RBT groups will have better retention of learning than the walking control group; i.e., the RBT groups will take fewer steps to respond to the novel perturbation than the walking control group one week post-training.

Secondary objectives are to compare the rate of adverse outcomes between groups, and to determine the effect of different intensities of RBT on the mechanisms underlying improved reactive stepping ability, functional balance, falls efficacy, and participation in daily activities.

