## 2.7 Analyses

One-way analysis of covariance (ANCOVA), with sex as a covariate, will be used to compare learning rates between the 3 groups. ANCOVA, controlling for the pre-training value, will be used to compare the following outcomes between the 3 groups at the post-training and retention time points: average number of steps, step initiation time, step execution time, step length, braking impulse, margin of stability, mini-BEST, and FES-I. Pre-planned contrasts will be used to compare outcomes between the high- and moderate-intensity groups, and between the two RBT groups combined and the walking control group. Alpha will be 0.05 for the primary outcome (learning rates), and adjusted for multiple comparisons using the Holm-Bonferroni method for secondary outcomes. Falls and quality of life data will be reported without inference so that these data can be used in meta-analyses and/or as pilot data for future studies.

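### The 80% power in section 2.6 belongs to the three-group test; on the same inputs primary hypothesis 1 (high vs moderate intensity) has about 8% power, while combined RBT vs walking has about 85%

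*Protocol*

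**What the plan says.** Section 1.2 gives finding the optimal training intensity as the purpose of the study. The first of its primary hypotheses is "Adaptation rate will be faster for high-intensity RBT than moderate-intensity RBT". The second is that the RBT groups adapt faster than the walking group.

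Section 2.6 derives the sample size for learning rate from one three-group quantity, lambda divided by Delta. It uses alpha 0.05, a "probability of a Type II error ( $\beta$ ) of 0.2", a tabulated lambda "of 9.64 was used", and expected learning rates of 0.4 (high), 2 (moderate) and 10 (walking). The spread is a single value: "From pilot data, we estimate a standard deviation of 9.7 for the learning rate". The result is "giving a target sample size of 17 per group or 51 participants total", raised to 21 per group (63 in total) for withdrawal. The section presents the three assumed rates as meaningfully different across the groups. It gives no power for any comparison between particular groups.

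Section 2.7 names an ANCOVA across the three groups and adds: "Pre-planned contrasts will be used to compare outcomes between the high- and moderate-intensity groups", together with a contrast of the two RBT groups combined against walking. On the significance level it says "Alpha will be 0.05 for the primary outcome (learning rates"), without stating whether tests are one- or two-sided.

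**The concern.** A three-group test can reach its target power because one group lies far from the other two. Here the walking mean of 10 is far from both RBT means, which differ from each other by only 1.6, or 0.165 of the stated SD. The 80% may therefore say almost nothing about the comparison that the trial was set up to make.

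If so, a reader of section 2.6 would credit hypothesis 1 with power it does not have. A significant overall result could be taken as evidence on intensity when it mainly shows that RBT differs from walking. A non-significant intensity contrast would be the likely result even if the assumed difference were exactly true, and would carry little information. Section 4.1 intends the results to guide clinicians on training parameters, so this is the comparison on which the practical message rests.

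**Working it through.** **Inputs.** From section 2.6: means 0.4, 2 and 10; SD 9.7; lambda 9.64; 17 evaluable and 21 recruited per group. From section 2.7: alpha 0.05 and the two contrasts. Assumed: two-sided tests, with one-sided results also shown.

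**1. The protocol's own figure.**
- Grand mean = (0.4 + 2 + 10)/3 = 4.133.
- Sum of squared deviations = 13.94 + 4.55 + 34.42 = 52.91.
- Delta = 52.91/9.7² = 52.91/94.09 = 0.562 (stated 0.56).
- n = 9.64/0.562 = 17.1, so the stated 17 reproduces.
- Power of the three-group test at 17 per group: 79.7% by noncentral chi-square (2 df), 77% by noncentral F.

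**2. Where Delta comes from.** The sum 52.91 splits exactly into the two planned contrasts.
- High vs moderate: 1.6²/2 = 1.28, which is 1.28/52.91 = 2.4%.
- Combined RBT (mean 1.2) vs walking: 8.8²/(1/2 + 1) = 51.63, which is 97.6%.

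As a check, set both RBT means to 1.2, so that intensity has no effect. Delta becomes 51.63/94.09 = 0.549 and n = 9.64/0.549 = 17.6. The calculation barely registers whether hypothesis 1 is true.

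**3. Power of each comparison at 17 per group** (noncentral t, 47 error df after adjusting for sex, two-sided 0.05).
- High vs moderate: SE = 9.7 × √(2/17) = 3.33; 1.6/3.33 = 0.48.
- Combined RBT vs walking: SE = 9.7 × √(1/34 + 1/17) = 2.88; 8.8/2.88 = 3.05.

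| Comparison | Difference | Power |
|---|---|---|
| High vs moderate (hypothesis 1) | 1.6 | 7.6% |
| Combined RBT vs walking (hypothesis 2) | 8.8 | 85% |
| High vs walking | 9.6 | 81% |
| Moderate vs walking | 8.0 | 65% |

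For high vs moderate, power is 8.2% if all 21 per group are evaluable. One-sided at 0.05 it is 12% (17 per group) or 13% (21 per group).

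**4. Scale of the shortfall.**
- For 80% power on hypothesis 1 (normal approximation, two-sided): n = 2 × (1.96 + 0.842)² × 94.09/1.6² ≈ 577 per group. This only shows the size of the gap; it is not a proposal.
- Smallest pairwise difference detectable with 80% power at 17 per group: 3.33 × (1.96 + 0.842) ≈ 9.3, against 1.6 assumed.

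**5. Sensitivity to the SD.** If the SD in the RBT groups were below 9.7 (assumed values, not in the document) and the contrast used the error of those groups, power for hypothesis 1 at 17 per group would be about:

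| SD in RBT groups | Power |
|---|---|
| 9.7 (as stated) | 8% |
| 5 | 15% |
| 3 | 33% |
| 1.6 | 81% |

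**The case against.** The calculation contains no arithmetic error, and it matches the first-named primary analysis, the three-group ANCOVA. What is missing is the power of a contrast. That stands. But section 2.6 offers its type II error as the justification for the primary outcome, and the first-listed primary hypothesis on that outcome does not have it. This is therefore more than a detail left to a later document.

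Three stronger readings are tempting, and the protocol does not support them.

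- *The trial is underpowered throughout.* A reader might infer this from the 8%. It is not so: the combined contrast that section 2.7 plans for hypothesis 2 has about 85% on the same inputs. The shortfall is specific to hypothesis 1.
- *The intensity contrast is bound to fail.* The 8% rests on one SD of 9.7 for every group. Section 2.6 does not say which group or population the pilot data came from, and an SD of 9.7 around an expected mean of 0.4 is hard to credit for the high-intensity group. A smaller SD in the RBT groups would raise the power, although it must fall to about 1.6 before 80% is reached.
- *Moving hypothesis 1 to log learning rate or to step counts would restore the power.* The protocol gives no SD on either scale. The three assumed values have a constant ratio of 5, but they are means. If learning rates were lognormal with those means and SD 9.7, the log-scale SDs would be about 2.5, 1.8 and 0.8, which are far from equal. The fitted rate is also not constrained to be positive, so its logarithm may not exist for every participant.

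Nor does any section say that a non-significant intensity contrast would be read as equal effectiveness. Section 4.1 discusses the expected positive result. The request on interpretation below is a precaution, not a correction of a stated error.

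**Conclusion.** The point holds, on the protocol's own numbers. The 80% in section 2.6 is the power of the three-group test (77 to 80% at 17 per group). Hypothesis 2, tested as the combined contrast, has about 85%. Hypothesis 1 has about 8% two-sided and no more than 13% one-sided, so the unstated sidedness does not change the conclusion. A significant overall test would mainly reflect RBT against walking and would leave the intensity question open.

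The figures assume the stated means, a common SD of 9.7 and no gain in precision from adjusting for sex. The assumption most able to change the result is the SD in the two RBT groups, and the protocol gives nothing with which to judge it.

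**What to change.** In section 2.6:

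- State that 80% refers to the three-group test of learning rates.
- Give the power of each planned contrast on the same inputs: about 8% for hypothesis 1 and about 85% for hypothesis 2, with the sidedness named.
- State which group or population the pilot SD of 9.7 came from and whether it applies to the RBT groups. If it does not, give the SD that does and recompute.

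In section 2.7, or in the statistical analysis plan, state that the high vs moderate difference will be reported with its confidence interval and that a non-significant result will not be read as equal effectiveness. At 17 per group and SD 9.7 the 95% interval would be roughly ±1.96 × 3.33 = ±6.5 around the estimate, about four times the assumed difference, which makes the limitation plain.

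Another scale or an analysis of step counts may be examined in the pilot data, but that is an option and not needed to correct the section.

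The cost is a look back at the pilot data, a few sentences of wording and a less favourable published power figure for hypothesis 1. No extra participants are needed.

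### The stated Type II error of 0.2 comes from a large-sample formula; for the ANCOVA F test actually planned, 17 per group gives about 77% omnibus power.

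*Protocol*

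**What the plan says.** Section 2.6 of the protocol sizes the trial on learning rate. The number per group is λ/Δ, where Δ is the sum of squared deviations of the group means from their overall mean, divided by the variance. The Type I error is "of 0.05, probability of a Type II error" "of 0.2; therefore", and from tables for three groups a λ "of 9.64 was used". On spread, "we estimate a standard deviation of 9.7 for the learning rate". The anticipated means are about 0.4, 2 and 10 for high-intensity, moderate-intensity and walking control. Δ is given as 0.56, "giving a target sample size of 17 per group or 51 participants total".

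The recruitment target follows: "To account for a ~20% rate of withdrawal", 21 per group or 63 in total are sought. The stopping rule is: "Enrolment will stop when 51 participants have completed the retention test, or 63 participants have been enrolled, whichever happens first".

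Section 2.7 fixes the primary analysis as a one-way ANCOVA of learning rate across the three groups with sex as covariate: "Alpha will be 0.05 for the primary outcome (learning rates").

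**The concern.** The sample-size formula and the planned test do not match. A fixed λ for a given number of groups, whatever the sample size, belongs to a chi-square test with known variance. An ANCOVA estimates the residual variance, and with about 50 participants that costs noticeable power. The stated Type II error would then be too small even if every planning assumption held. The ratio λ/Δ is also slightly above 17, so 17 is a rounding down.

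At stake is how a non-significant omnibus result is read. A reader would take the chance of missing the planned differences to be 20%, when for the specified test it is about 23%.

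**Working it through.** **Inputs.** Means 0.4, 2 and 10; SD 9.7; λ 9.64; Type I error 0.05; Type II error 0.2; 17 per group; about 20% withdrawal; 63 enrolled (all section 2.6). ANCOVA with one covariate at 0.05 (section 2.7). Equal group sizes are assumed, in line with the equal per-group targets.

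**1. Reproduce the protocol's figure.**
- Overall mean: (0.4 + 2 + 10)/3 = 4.133.
- Squared deviations: 13.94 + 4.55 + 34.42 = 52.91.
- Δ = 52.91/9.7² = 52.91/94.09 = 0.5623. The protocol's 0.56 is confirmed.
- λ/Δ = 9.64/0.5623 = 17.14, or 9.64/0.56 = 17.21. The protocol's 17 is reproduced, rounded down.

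**2. Identify λ.** Solving for the noncentrality at which a 2-df chi-square test at 0.05 has 80% power gives 9.635. The tabulated 9.64 is therefore the large-sample value.

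**3. Power at 17 per group by the protocol's own method.** The noncentrality is 17 × 0.5623 = 9.56. The noncentral chi-square with 2 df gives 79.7%. Rounding down therefore costs 80.0 − 79.7 = 0.3 point.

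**4. Power at 17 per group for the planned test.** Error df = 51 − 3 group means − 1 covariate = 47. The noncentral F with 2 and 47 df and the same noncentrality gives 76.9%. Moving from chi-square to F costs 79.7 − 76.9 = 2.8 points. The total shortfall is 3.1 points, and the Type II error is 1 − 0.769 = 0.231. Using the rounded Δ of 0.56 gives 76.7%.

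**5. Power at other sizes** (Δ = 0.5623, error df = 3n − 4):

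| n per group | Chi-square | ANCOVA F |
|---|---|---|
| 16.8 (63 × 0.8 = 50.4 in total) | 79.2% | 76.3% |
| 17 | 79.7% | 76.9% |
| 18 | 82.0% | 79.5% |
| 19 | 84.2% | 81.9% |

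Rounding up to 18 would satisfy the protocol's own formula but still leave the F test just short. The smallest equal group size that reaches 80% is 19, or 57 analysed.

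**6. Attrition.** At exactly 20%, 63 × 0.8 = 50.4 completers, which is 0.6 below 51. 63 enrolled yields 51 if withdrawal is 12/63 = 19.0%. At exactly 20% the power is 76.3%, a further 0.6 point lower.

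**The case against.** - **The method is a recognised one.** λ/Δ comes from a cited textbook, and the protocol says only that the size was estimated this way. That is fair, and using the formula is not a blunder. The Type II error it yields is still not that of the F test which section 2.7 specifies.
- **Uncertainty in the inputs is larger than the correction.** At 17 per group the F test has about 83% power if the SD is 9.0 and 74% if it is 10.0. This limits how much weight three points should carry. It does not make the stated figure right at the stated SD.
- **Sex may explain some variance.** If it explained about 7% of the within-group variance, 17 per group would reach 80%. The protocol gives no such figure and takes no credit for it. Zero is also an assumption, so it should be stated.
- **The number analysed may exceed 51.** The stopping rule counts retention-test completers, and someone who trained but missed the retention test might still supply a learning rate. With 55 analysed, power would be 80.3%. The protocol does not plan on this gain.

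A reader might also infer three stacked errors: a wrong rounding, a wrong formula and an inadequate attrition allowance. The document does not support that. The rounding costs 0.3 point, and an SD of 9.65, which prints as 9.7, gives Δ = 52.91/93.12 = 0.568 and λ/Δ = 16.97. So 17 may simply reflect unrounded inputs. The attrition rate is given only as approximate, and 19.0% falls within it. The shortfall at exactly 20% is less than one participant.

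**Conclusion.** The point holds, in a limited form. For the ANCOVA F test planned in section 2.7, the design in section 2.6 has omnibus power of about 77% with 51 analysed, so the Type II error is about 0.23 rather than 0.2. Nearly all of the gap comes from using a chi-square λ for a test with 47 error df. Rounding is a minor contributor and attrition is not an error.

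The figure rests on the protocol's own means and SD, equal groups, a common SD, 51 participants in the primary analysis, and no variance explained by sex. It concerns the omnibus comparison only. The misstatement is modest but can be checked from the protocol alone, and it sits in the justification for the primary outcome, so it should be corrected.

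**What to change.** In section 2.6, keep the targets of 51 completers and 63 enrolled. Restate the Type II error as about 0.23 (power about 77%) with 51 analysed, calculated from the noncentral F with 2 and 47 df, and say that sex is assumed to explain no variance. Adding that power is about 76% if exactly 20% of 63 withdraw would make the attrition statement complete. This changes one figure and adds a sentence or two. It needs no extra participants and no change to conduct or analysis.

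If a Type II error of 0.2 is to be kept, the matching figure is 19 completers per group (57 in total, 81.9% power). At 20% withdrawal that means 19/0.8 = 23.75, so 24 enrolled per group or 72 in total: nine more than now planned. Both limits in the stopping rule would have to change to match.

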## 1. INTRODUCTION

### 1.1 Background and rationale

Remaining active after stroke is essential to recovery, maintaining quality of life, and reducing secondary stroke risk. However, impaired balance control post-stroke increases fall risk, contributes to fear of falling, and reduces overall mobility, activity, and community integration. Therefore, effective interventions to improve balance control and reduce fall risk are essential to ongoing recovery and quality of life post-stroke. However, while there is unequivocal evidence that exercise, specifically balance training, is the most effective intervention for preventing falls in older adults without stroke, it is unclear if exercise prevents falls after stroke.

Effective balance reactions (e.g., reactive stepping) are essential to avoid falling following a loss of balance, or balance perturbation. Reactive balance training (RBT), where clients experience repeated balance perturbations, is a novel type of exercise that aims to improve control of balance reactions. We found that RBT improves reactive stepping ability in people with stroke. Our recent meta-analysis found that RBT reduces rate of falls in daily life by ~40% among older adults and people with neurologic conditions, including stroke.

Clinicians are unsure how to optimally prescribe RBT. Exercise is often prescribed considering frequency, intensity, time, and type; these parameters are interdependent. For example, as intensity increases, frequency or time can decrease to achieve similar benefits. Clinicians report that limited time in rehabilitation services and competing rehabilitation goals and priorities mean that there is little time available to include RBT in a client's treatment plan. Therefore, it would be valuable to know if a short duration of high-intensity RBT can improve reactive balance control post-stroke. However, it is possible that people with stroke would not tolerate high intensity perturbations and, therefore, require lower-intensity but long-duration RBT. No study has directly compared different RBT training intensities among people with stroke.

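### Enrolment stops on 51 completers pooled over the three groups, although the sample size is 17 per group, so it can close with a group short and planned places unused (minor)

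*Protocol*

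**What the plan says.** Protocol section 2.6 derives the sample size per group, "giving a target sample size of 17 per group or 51 participants total". It then allows for dropout: "To account for a ~20% rate of withdrawal", "we will aim to recruit 21 participants per group, or 63 participants total". The withdrawal rate is a single figure, not split by group. The section ends with the operating rule: "Enrolment will stop when 51 participants have completed the retention test, or 63 participants have been enrolled, whichever happens first". That rule has no minimum for any group.

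Section 2.3 uses blocks of 6 or 9, stratified by sex. This balances the numbers randomised, not the numbers who complete. Figure 1 in section 2.1 places baseline on Day 1 and the retention test on Day 12, so some enrolled participants may still be in progress when the 51st completes.

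**The concern.** The requirement is per group and the stop is on the total. If enrolment ends exactly at the 51st completer, all three groups have 17 only when the split is 17/17/17. Any other split leaves at least one group short, and the sentence closes enrolment even though part of the planned 63 has not been used. At stake is whether the rule delivers the group sizes on which the calculation rests. This rule is stated in the protocol itself; it is not a detail left to an analysis plan.

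**Working it through.** **1. The plan's own figure.** Inputs from section 2.6: means 0.4, 2 and 10, standard deviation 9.7, λ = 9.64.
- Mean of means = 12.4/3 = 4.133.
- Squared deviations: 13.94 + 4.55 + 34.42 = 52.91.
- Δ = 52.91/9.7² = 52.91/94.09 = 0.562 (stated 0.56).
- n = λ/Δ = 9.64/0.562 = 17.1, given as 17.
- Dropout: 17/0.8 = 21.25 per group and 51/0.8 = 63.75 in total, given as 21 and 63.

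The stated figures reproduce, apart from rounding down. At 20% withdrawal, 63 × 0.8 = 50.4 completers are expected, slightly under 51.

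**2. What follows without simulation.** Suppose nobody is in progress at the stop. Then the pooled rule ends with exactly 51 completers, or at the cap with at most 51. All groups can reach 17 only at 17/17/17. Under a per-group rule with the same cap, completers are never lost by enrolling on, so its chance of success is the highest that any rule capped at 63 can reach.

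**3. Simulation.** Sex-stratified blocks of 6 or 9, independent withdrawals, 4,000 runs per scenario. Assumptions not in the protocol: a 60/40 sex mix, the number in progress at the stop (0, 3 or 6, all followed to their test), and withdrawal rates other than 20%.

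| Withdrawal, every group | In progress | Stops before 63 | Stops before 63 with a group below 17 | All groups ≥17: pooled rule | All groups ≥17: per-group rule |
|---|---|---|---|---|---|
| 20% | 0 | 40% | 37% | 4% | 18% |
| 20% | 3 | 14% | 7% | 15% | 19% |
| 20% | 6 | 2% | 0.4% | 18% | 17% |
| 15% | 0 | 78% | 71% | 7% | 48% |
| 15% | 3 | 46% | 23% | 35% | 48% |
| 15% | 6 | 13% | 2% | 46% | 48% |
| 10% | 0 | 98% | 86% | 11% | 80% |
| 10% | 3 | 87% | 33% | 57% | 81% |
| 10% | 6 | 52% | 5% | 78% | 79% |

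Repeat runs agree to within about two percentage points. By step 2 the per-group rule cannot do worse than the pooled one, so 18% against 17% is simulation noise.

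Given an early stop at 20% withdrawal, the share with a group below 17 is 0.365/0.396 = 92% with nobody in progress, 0.073/0.136 = 54% with three, and 0.004/0.024 = 17% with six. With nobody in progress, an early stop leaves on average about 3 places unused at 20% withdrawal, 4.3 at 15% and 6.5 at 10%.

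**4. Unequal withdrawal (assumed splits, high/moderate/walking).** All groups reaching 17, pooled against per-group rule:
- 20/10/5%: 5% against 51–54% with nobody in progress; 33% against 52% with three.
- 25/5/5%: 3% against 36%; 18% against 35%.
- 30/20/10%, which averages 20%: 1% against 10%; 7% against 10%.

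**5. Power of the three-group test** (noncentral F, the protocol's means and standard deviation). It is 0.769 at 17/17/17. Mean power, pooled against per-group rule, nobody in progress: 0.750 against 0.757 at 20% withdrawal, 0.764 against 0.779 at 15%, 0.767 against 0.789 at 10%. At 20/10/5% it is 0.779 against 0.804. The gains are 0.007, 0.015, 0.022 and 0.025. With six in progress they are at most 0.005 under equal withdrawal.

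**6. Enrolment.** Mean enrolled, nobody in progress: 61.7 against 62.6, 59.6 against 61.7, and 56.7 against 59.5 at 20%, 15% and 10%. That is 0.9, 2.1 and 2.8 more. With three in progress the differences are 0.2, 0.9 and 2.0. At 20/10/5% with nobody in progress it is 61.0 − 57.7 = 3.3.

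**The case against.** The case against is strong on size.

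- **The cap, not the pooled count, drives most of the shortfall at the planned rate.** At 20% withdrawal, 63 are enrolled in about 60% of runs with nobody in progress and in 86–98% with three to six. The per-group rule itself succeeds in only about 18%. This stands.
- **Participants in progress complete after the stop.** With six in progress the gap all but closes. Nobody in progress is the assumption least favourable to the plan, and the protocol gives no recruitment pace. This stands, so the range has to be shown. A reader might infer that the rule almost never yields 17 per group. That is not general: at 10% withdrawal with three to six in progress it does so in 57–78% of runs.
- **Little power is lost.** This stands. The high-versus-moderate contrast has power of about 7.6% at 17/17/17 under the protocol's own means. At 20/10/5% it is 7.5% under the pooled rule and 7.6% under the per-group rule.
- **Unused places would refill a depleted group only partly,** because blocking spreads them over all groups. This stands: under the first two unequal splits, mean high-intensity completers rise from 15.4 to 16.3 and from 14.4 to 15.5.
- **17 per group is called a target, and 51 is the protocol's own total.** This makes the rule loose rather than contradictory. It does not remove the mismatch between a per-group requirement and a pooled stop.

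Two stronger readings are tempting. The first is that the high-intensity group will be the short one. Section 1.1 says only that "it is possible that people with stroke would not tolerate high intensity perturbations". It makes no statement about completion. Section 3.2.1 reports similar adverse events in the training and control groups of earlier work and says very high intensities will be avoided, and section 2.8.2 lets the physiotherapist modify sessions. The second is that the harms comparison suffers. Section 2.8.2 has adverse outcomes observed in every session and asked about at the next, so someone who withdraws still contributes harms data.

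**Conclusion.** The point holds as a minor one. The stopping rule does not secure the per-group number on which the sample size rests. When the 51-completer condition is met first, a group is often below 17 with planned places left: in about 92% of such stops at 20% withdrawal with nobody in progress, and 54% with three. The benefit of a per-group rule lies mainly where overall withdrawal is below the planned 20%, whether or not it is even across groups, and where few participants are in progress. At about 20% neither rule reliably gives 17 per group. The power gain is about 0.00–0.03. The size rests on the assumed sex mix, withdrawal pattern and number in progress. The mismatch itself rests on the text alone. The protocol does not support any claim about which group falls short or about loss of harms information.

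**What to change.** Replace the last sentence of section 2.6 with a rule that enrolment closes once each of the three groups has at least 17 retention-test completers, or once 63 people have been enrolled, whichever is sooner. Add that 17 per group is a target which the cap of 63 may not reach.

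The principal investigator can apply the rule. Under section 2.3 that role performs the allocation centrally and does not recruit, so assessors need not see group counts.

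The cost is one sentence and on average about 0–3 further enrolments, all within the planned 63. Dropping the 51-completer condition and enrolling to 63 is an equally simple alternative. It costs more where withdrawal is low: 63 − 56.7 = 6.3 more than the present rule at 10% withdrawal with nobody in progress.
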